## Abstract

**Background:**

Diarrhea is a common adverse reaction in patients with cancer receiving chemotherapy, for which there is currently no effective method of treatment. Shengjiang Xiexin decoction (SXD), a classic traditional Chinese medicine (TCM) formula, has shown efficacy in alleviating irinotecan-induced diarrhea in preliminary clinical studies. The current study is designed to assess the efficacy and safety of SXD for prophylaxis against irinotecan-induced diarrhea. Additionally, we employ a new approach to analyze and evaluate the data based on the patients’ uridine diphosphate glucuronosyltransferase 1A1 (UGT1A1) genotype, which predicts the risk of diarrhea.

**Methods and design:**

A prospective, double-blind, randomized, placebo-controlled trial will be conducted in patients with small cell lung cancer (SCLC) from five hospitals in China. For this study, 100 irinotecan-naïve patients will be randomly allocated to either the SXD or placebo arms in a 1:1 ratio. Stratified randomization will be used to divide subjects by UGT1A1 genotype into groups with differing risk of diarrhea. The trial will consist of two cycles of chemotherapy with 14 days of oral administration of SXD or placebo administered beginning between 3 days before and up to 11 days after initiation of each chemotherapy cycle. The primary study outcome is the incidence of diarrhea. Secondary outcomes include the degree of diarrhea, the degree of neutropenia, the rate of alterations in chemotherapy regimens, the amount of antidiarrheal drug taken, the rate of hospitalization, and evaluation of chemotherapy efficacy.

**Discussion:**

This study is the first to use the UGT1A1 genotype to stratify patients into groups based on their risk of diarrhea, and to provide a complete assessment of chemotherapy-related diarrhea (CRD), including records of diarrhea duration, grading the severity of diarrhea, and evaluating concomitant symptoms. Study results will provide high-level clinical evidence on the use of SXD as prophylaxis for CRD.

**Trial registration:**

Chinese Clinical Trial Register: ChiCTR1800018490. Registered on 20 September 2018. Retrospectively registered. http://www.chictr.org.cn/edit.aspx?pid=25250&htm=4c

## Background

Chemotherapy-related diarrhea (CRD) is a common adverse reaction in oncotherapy [1]. Treatment often requires reducing the chemotherapeutic dose and delaying or interrupting the chemotherapy schedule due to severe and potentially life-threatening dehydration and electrolyte disruption [2]. When that happens, patients often require hospitalization to replenish fluids and electrolytes, which increases patients’ medical expenses. As a consequence, the effects of chemotherapy may be attenuated and the patient’s financial burden may be increased. Irinotecan is a first-line or second-line therapeutic agent for small cell lung cancer (SCLC) that often induces diarrhea. The incidence of all degrees of attendant diarrhea is 50–80% [3]; the incidence of severe diarrhea (grade 3–4) is 11–32 %[4, 5]. In patients with the UGT1A1 gene mutation, the risk of severe diarrhea increases significantly [6].

The mechanism underlying irinotecan-induced diarrhea is not yet clear [7]. It is accepted that the UGT1A1 gene polymorphism test can be used to predict the risk of diarrhea based on the metabolic sequelae of irinotecan in vivo [8]. A study of the correlation between UGT1A1 gene polymorphisms in Chinese patients and irinotecan toxicity showed that UGT1A1*28 genotypes are more involved in the development of diarrhea. Thus, the incidence of severe diarrhea in patients accepting irinotecan with wild type UGT1A1*28, heterozygous UGT1A1*28, and homozygous UGT1A1*28 was 1.28% (1/78), 31.5% (6/19), and 66.7% (4/6), respectively [9]. It is thus clear that the UGT1A1 gene is important in irinotecan-induced diarrhea. However, previous studies rarely included the UGT1A1 genotype as an influencing factor when grouping, which will produce selection bias and inaccurate results.

The currently recommended treatments for CRD, which are based on specialist consensus and guidelines, have important deficiencies, such as dubious efficacy [10]. easy invalidation [11], or accompanying side effects [12, 13], and none have been approved for clinical benefit. Effective prophylaxis is also lacking.

SXD is recorded in the traditional Chinese medicine (TCM) classic “Treatise on Febrile Diseases” from 2000 years ago. It is typically administered for the treatment of inflammatory bowel disease [14]. In our previous study, we found that SXD significantly reduced irinotecan-induced gastrointestinal toxicity, especially in the presence of the UGT1A1 mutation. It is well-known that toxicity with the mutant type is more serious than with the wild type. However, no significant differences in toxicity were noted between the mutant and the wild type when SXD was administered (*P* > 0.05) [15]. In addition, we established a model of diarrhea in the rat to explore the possible mechanisms of the antidiarrheal action of SXD. We found that treatment with SXD was associated with an inhibitory effect on intestinal apoptosis combined with a promotional effect on intestinal cell proliferation, owing to enhanced maintenance of intestinal stem cells (ISCs) [16]. Another animal study showed that SXD altered the pharmacokinetics of irinotecan and its metabolites to alleviate irinotecan-induced diarrhea, specifically by reducing the hepatic transporters multidrug resistant-associated protein-2 (Mrp-2) and P-glycoprotein (P-gp) and by upregulating UGT1A1 in the liver and jejunum [17].

We designed this study because there have been no large-scale clinical trials and little high-level clinical evidence on the treatment and prevention of CRD. The aim of our study is to evaluate the efficacy and safety of SXD prophylaxis against irinotecan-induced diarrhea in patients with SCLC, specifically that involving the UGT1A1 mutation as determined by genetic analysis before initiating chemotherapy. In this way, we hope to balance the groups by reducing the bias otherwise caused by different levels of risk of CRD in different genotypes. Meanwhile, we will also evaluate whether SXD has an impact on the efficacy of chemotherapy.

## Methods and designs

### Study design

The study will be conducted in five hospitals in Beijing, China, including China-Japan Friendship Hospital (Ethical Approval Document No. 2018–82-K57), Beijing Friendship Hospital Affiliated with Capital Medical University (2019-P2–016-02), Beijing Hospital of TCM Affiliated with Capital Medical University (2018BL-057-02), Wangjing Hospital of China Academy of Traditional Chinese Medicine (WJEC-KT-2018-045-P001), and Beijing Chaoyang Hospital Affiliated with Capital Medical University (2018-KE-313).

The study design flow chart is shown in Fig. 1. The trial will use stratified random grouping. Eligible subjects will first undergo UGT1A1 gene testing and be stratified to one of two levels, low or moderate-to-high risk of CRD, after which they will be randomly allocated to the SXD treatment cohort or the placebo cohort within their risk group. Patients will be excluded if UGT1A1 testing fails for any reason. The trial will include two cycles of chemotherapy (21 days per cycle), and each cycle will consist of 14 days of oral administration of SXD or placebo beginning 3 days before initiation of chemotherapy, with a follow-up visit from the initiation of chemotherapy. The trial schedule, including patient enrollment, interventions, and outcome measurements is shown in Fig. 2.

**Fig. 1 Fig1:**
[figure not shown]
The study design flow chart. SXD, Shengjiang Xiexin decoction; d, day

**Fig. 2 Fig2:**
[figure not shown]
The schedule of study phases; chemo, chemotherapy; CT, computed tomography; MRI, magnetic resonance imaging; SXD, Shengjiang Xiexin decoction

### Sample size

The study proposes that SXD can reduce the occurrence of irinotecan-related diarrhea in patients with SCLC, which was the working hypothesis we used to calculate sample size. This study was designed as a superiority trial and sample size calculations are based on the primary outcome measurement - the incidence and percentage of CRD. Based on the results of our preliminary observational study and previous literature [18], the incidence of CRD is 37.5% (6/16) with SXD and 63.4% without SXD, respectively.

In our study, the ratio of subjects will be 1:1 in both the SXD and control groups. Sample size calculations were performed using PASS software, version 15.0, for a superiority test for two independent, randomized samples. With a significance level of 5% (α), a two-sided test, and power of 80% (1 − β), the required sample size was determined to be approximately 40 per group. Considering an estimated dropout rate of 20%, 50 subjects will be required per group, giving a total of 100 subjects.

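### The sample size of about 40 per group does not follow from its own inputs, which require about 58, so the trial falls short of its stated 80% power

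*Protocol article*

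**What the plan says.** The whole calculation is in the Sample size section of the protocol article.

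- Design and endpoint: "This study was designed as a superiority trial", and "sample size calculations are based on the primary outcome measurement - the incidence and percentage of CRD".
- Rates: "the incidence of CRD is 37.5% (6/16) with SXD and 63.4% without SXD, respectively".
- Error rates: two-sided 5% significance level and 80% power, computed in PASS 15.0 as a comparison of two independent samples.
- Allocation: "the ratio of subjects will be 1:1 in both the SXD and control groups". The abstract agrees.
- Result: "the required sample size was determined to be approximately 40 per group".
- Dropout: "Considering an estimated dropout rate of 20%, 50 subjects will be required per group, giving a total of 100 subjects".

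The Statistical analysis section plans a chi-square or Fisher's exact test for the incidence of diarrhea. The primary analysis is by intention to treat on all participants, with missing primary data filled by the last recorded value.

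**The concern.** Every input needed for the calculation is printed next to the result, so the result can be checked without outside sources. A difference of 25.9 points around a mean rate of about 50% normally needs well over 40 per group for 80% power in a two-sided 5% test.

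The target of 100 patients rests on this paragraph alone. If the figure is too low, the chance of missing a real effect of the planned size is larger than the one in five that the reader is told. A non-significant result could then be taken as stronger evidence against SXD than it is.

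**Working it through.** **Inputs** (Sample size section): p1 = 0.375, p2 = 0.634, difference d = 0.259, 1:1 allocation, two-sided alpha 0.05 (z = 1.960), power 80% (z = 0.8416). No superiority margin is stated, so I take it as zero. A margin above zero would only raise the requirement.

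**Step 1. Try to reproduce 40.** The pooled-variance formula is

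n = [z_α √(2 p̄(1−p̄)) + z_β √(p1(1−p1) + p2(1−p2))]² / d²

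with p̄ = (0.375 + 0.634)/2 = 0.5045.

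- 2 p̄(1−p̄) = 2 × 0.5045 × 0.4955 = 0.49996; square root 0.7071.
- p1(1−p1) + p2(1−p2) = 0.2344 + 0.2320 = 0.4664; square root 0.6829.
- n = (1.960 × 0.7071 + 0.8416 × 0.6829)² / 0.259² = (1.3858 + 0.5748)² / 0.06708 = 57.3, so **58 per group**.

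The stated 40 is not reproduced.

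**Step 2. Try other standard versions** (n per group, rounded up).

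| Method | Two-sided 5% | One-sided 5% |
|---|---|---|
| Unpooled Z | 55 | 43 |
| Pooled Z | 58 | 46 |
| Arcsine | 58 | 46 |
| Log odds ratio | 60 | 48 |
| Continuity-corrected | 65 | 53 |

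None gives 40. The lowest, 43, needs a one-sided test, which contradicts the text.

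**Step 3. Check the dropout step.** 40 / (1 − 0.20) = 50. This is correct, so the fault lies in the 40.

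**Step 4. Power that the planned numbers deliver** at the stated rates, two-sided 5%. By normal approximation,

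power = Φ{[d√n − z_α √(2 p̄(1−p̄))] / √(p1(1−p1) + p2(1−p2))}

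- n = 40: (0.259 × 6.325 − 1.3858) / 0.6829 = 0.369, and Φ(0.369) = 0.644.
- n = 50: (0.259 × 7.071 − 1.3858) / 0.6829 = 0.652, and Φ(0.652) = 0.743.

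Exact figures come from summing the binomial probabilities of all outcome pairs that the test rejects.

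| n per group | Normal approximation | Chi-square, exact | Fisher, exact |
|---|---|---|---|
| 40 | 64.4% | 66.9% | 58.3% |
| 50 | 74.3% | 76.4% | 69.6% |
| 58 | 80.5% | 80.8% | 75.2% |

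A one-sided 5% test at 40 per group has power 75.7%, so that reading does not give 80% either.

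**Step 5. What effect 40 or 50 per group can detect with 80% power.** Solving the Step 1 formula for the SXD rate with control at 63.4%:

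- n = 40: SXD rate 32.6%, a difference of 30.8 points.
- n = 50: SXD rate 35.7%, a difference of 27.7 points.

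Alternatively, with SXD held at 37.5%, 40 per group would need a control rate of about 68%. The document states neither 32.6% nor 68%.

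**Step 6. What 80% power would take at the stated rates.** 58 analysed per group. With the protocol's own dropout allowance, 58 / 0.80 = 72.5, so 73 per group and 146 in total.

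**Step 7. Sensitivity to the SXD rate.** This is separate from the arithmetic error. The 37.5% is 6/16, with an exact 95% confidence interval of 15% to 65%. If the true rate were 45% (my illustration), power by normal approximation would be 38% at 40 per group and 45% at 50.

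**The case against.** The strongest reply is that the primary analysis is by intention to treat with carried-forward values, so all 50 per group count and the 40-evaluable case is too pessimistic. This is fair as far as it goes. Missing a real effect more than one time in three applies to 40 analysed per group. With 50 it is about one in four by chi-square and three in ten by Fisher, against a stated one in five. The same argument makes 146 the upper end of a range, because 58 randomised and analysed per group (116 in total) would nominally suffice. It does not restore 80%, since 50 per group still falls short under both planned tests. It may also flatter the power if values carried forward from dropouts dilute the effect.

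A second reply is that a one-sided unpooled calculation gives 43, which could loosely be called about 40, so a one-sided run may have been mislabelled. That is conjecture. It contradicts the stated two-sided test, and the paragraph would still be wrong.

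A third is that stratification by UGT1A1 genotype gains precision. The calculation is described as a plain two-sample comparison, and the planned tests are unstratified.

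Nor is this detail that an article may leave to a fuller document, because the printed inputs and the printed result disagree. It is true that the sidedness and the analysis tests are already stated; only the test statistic used in PASS is not. The uncertainty in 6/16 bears on whether the assumption is optimistic. It does not show that 40 was miscalculated.

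**Conclusion.** The concern holds. The printed inputs require about 58 evaluable per group (55 to 65 across standard two-sided methods), not 40, a shortfall of 15 to 25 per group. At the protocol's own rates, power is 58% to 67% with 40 analysed per group and 70% to 76% with all 50, depending on the test. The stated 80% is not met in either case, so the conclusion does not depend on the dropout assumption. It assumes a zero superiority margin and takes the stated rates at face value. This must be corrected, because the justification for N=100 is wrong as written.

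**What to change.** Correct the Sample size paragraph in one of two ways, keeping N=100:

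- Restate the power at 37.5% versus 63.4%, two-sided 5%: about 64–67% by chi-square with 40 evaluable per group and 74–76% if all 50 are analysed. Give the Fisher figures too (58% and 70%), since the Statistical analysis section allows that test.
- Or state the difference detectable with 80% power against a control rate of 63.4%: about 31 points at 40 per group and 28 points at 50.

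Name the test statistic behind the calculation and confirm that it is two-sided. If PASS was run with other inputs, print those. I would add a sentence saying that, at this power, a non-significant result is inconclusive.

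The cost is rewording and a less favourable stated power; no extra patients are needed. If the sponsor prefers to keep 80% at the stated rates, the target becomes 58 analysed per group: 116 in total if everyone randomised is analysed, up to 146 with the 20% dropout allowance. That figure is by normal approximation or chi-square; Fisher's test at 58 per group gives 75%.

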### Inclusion and exclusion criteria

The inclusion criteria are as follows:
Patients with SCLC diagnosed by pathology testing;Irinotecan-naïve subjects who will be undergoing chemotherapy with irinotecan for the first time;No chemotherapy administered in the 3 months before patient enrollment;Age range between 18 and 70 years;Body mass index (BMI) > 20 kg/m^2^ and < 30 kg/m^2^;Patients with a score of 0–2 on the Eastern Cooperative Oncology Group (ECOG) assessment;Estimated patient survival duration ≥ 6 months;Patients with no heart, liver, kidney, or other major organ dysfunction, and the following laboratory values: neutrophils > 1.5 × 10^9^/L; platelets > 100 × 10^9^/L; hemoglobin > 90 g/L; bilirubin within normal limits or < 1.5 × the upper limit of normal (ULN); aspartate aminotransferase (AST)/alanine aminotransferase (ALT) < 2.5 × ULN; serum creatinine < 1.5 × ULN; endogenous creatinine clearance (CCR) ≥ 60 mL/min (calculated using the Cockcroft-Gault formula);Patients able to fully understand the aims and parameters of this study and provide signed, informed consent.

The exclusion criteria are as follows:
Patients with diarrhea caused by primary diseases (such as acute and chronic enteritis or inflammatory bowel disease), radioactive enteritis, long-term use of laxatives or drugs resulting in diarrhea (including antibiotics);Pelvic radiotherapy administered in the 2 weeks before study initiation;Intolerance to chemotherapy due to serious organic diseases or infections, such as heart, lung, or kidney failure in a decompensated stage;Patients whose UGT1A1 gene cannot be assessed;Pregnant or lactating women;Patients participating in other clinical trials currently or within the 4 weeks before study initiation;History of diagnosed psychiatric condition that may affect the patient’s ability to understand the study parameters and provide informed consent.

### Recruitment of subjects

Recruitment will mainly be conducted by means of posters and online advertisements. Posters will be displayed in the outpatient clinics and inpatient wards of each center, and the advertisements will be placed on each center’s website. Both the posters and advertisements will include the study profile, inclusion/exclusion criteria, interventions, and contact information. Physicians at each center will identify prospective patients. After their eligibility is confirmed, they will sign informed consent forms before they are enrolled.

### Subject withdrawal criteria

Study participation will be terminated if:
A severe adverse event (AE) occurs during chemotherapy;The chemotherapy schedule requires modification because of severe adverse reactions to chemotherapy;Subjects do not comply with this study’s requirements.

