#### Secondary outcomes

Secondary outcomes include the degree of diarrhea, degree of neutropenia, incidence of chemotherapy regimen alterations, amount and dose of antidiarrheal drugs taken, incidence of hospitalization for diarrhea, and evaluation of chemotherapy efficacy.

Each participant will be supplied with a diary in which they will be instructed to record the time, duration, and coexisting symptoms of diarrhea. The information will then be reported to the researchers. The grade of diarrhea will be assessed for each chemotherapy cycle, and the most serious grade for each participant will be recorded to compare the difference in grades between the SXD and placebo cohorts. The diarrhea grading criteria used will be in compliance with the Common Terminology Criteria for Adverse Events (CTCAE), Version 5.0, released by the National Cancer Institute (NCI), which is detailed in Table 2. In addition, to completely evaluate each episode of diarrhea, participants will be instructed to record in detail the duration of diarrhea and the presence of coexisting symptoms, such as stomachache, abdominal distension, and cramps.

**Table 2 Tab2:** Diarrhea grading criteria

Grade of diarrhea	Definition
**Grade 1**	Increase of < 4 stools per day from baseline; mild increase in ostomy output compared to baseline
**Grade 2**	Increase of 4–6 stools per day from baseline; moderate increase in ostomy output compared to baseline; limiting instrumental ADL
**Grade 3**	Increase of ≥ 7 stools per day from baseline; hospitalization indicated; severe increase in ostomy output compared to baseline; limited self-care in ADL
**Grade 4**	Life-threatening consequences; urgent intervention indicated
**Grade 5**	Death

*ADL* activities of daily living

The development of diarrhea can affect the chemotherapy dose, duration, and schedule. Therefore, alterations in the chemotherapy schedule will be calculated in each group, including dose reductions, treatment postponement or termination, and other alterations in the preplanned chemotherapy regimen. If serious diarrhea occurs, antidiarrheal drugs and even hospitalization may be required, as determined by the recommended guidelines and expert consensus. The amounts and doses of antidiarrheal drugs prescribed and the incidence of hospitalization will be recorded. Common antidiarrheal drugs are loperamide and berberine hydrochloride [21, 22].

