We will also evaluate whether SXD affects the efficacy of chemotherapy. When enrolling in the trial, eligible patients will complete the following baseline examinations: blood tumor markers (neuron-specific enolase (NSE) and pro-gastrin-releasing peptide (Pro-GRP)), chest computed tomography (CT), abdominal ultrasound, head magnetic resonance imaging (MRI), and a bone scan. After two cycles of chemotherapy, these examinations will be performed again and the Response Evaluation Criteria in Solid Tumors (RECIST1.1) will be used to evaluate the result.

Safety outcomes

The safety outcomes include AEs related to chemotherapy and SXD. Hematologic toxicity is a common AE related to the administration of irinotecan plus cisplatin [23]. Therefore, routine blood tests, including quantification of leukocytes, neutrophils, hemoglobin, and blood platelets, will be carried out before and after the day of the chemotherapy infusion (days 1 and 8 in a 21-day cycle). In addition, hepatic and renal function, blood clotting function, and electrocardiograms will be recorded at the same time. If the results are obviously abnormal, or if other severe chemotherapy-related adverse reactions occur, the chemotherapy schedule will be modified as required.

If any serious AEs related to SXD administration occur during the trial, the investigator will immediately provide the necessary diagnosis and treatment, and will report each incident to the study principal investigator within 24 h. All AEs will be surveyed and recorded in detail by an independent clinical research associate (CRA) until the participants recover to a stable condition.

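### The withdrawal criteria end study participation, not just study product, which truncates the secondary outcomes and lets patients who leave before any diarrhea be counted as event-free

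*Protocol article*

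**What the plan says.** Subject withdrawal criteria opens with "Study participation will be terminated if" and lists three triggers:

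- "A severe adverse event (AE) occurs during chemotherapy"
- "The chemotherapy schedule requires modification because of severe adverse reactions to chemotherapy"
- "Subjects do not comply with this study’s requirements"

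Severe diarrhea is not exempted from the first trigger.

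Other sections treat the same events as things seen and counted within the trial. Secondary outcomes lists degree of diarrhea, degree of neutropenia, regimen alterations, antidiarrheal use, hospitalization for diarrhea and chemotherapy efficacy, and says that "alterations in the chemotherapy schedule will be calculated in each group". Safety outcomes says that after clearly abnormal results or other severe reactions "the chemotherapy schedule will be modified as required". Quality control has two chief oncologists change regimens where needed. Response is assessed after two cycles, and the primary outcome window also closes only when both cycles are complete.

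Statistical analysis adds four rules. The primary outcome is analysed by intention to treat in all participants. Missing primary data are filled by carrying the last record forward. Secondary outcomes rest on the per-protocol set (PPS), restricted to patients who adhere strictly and complete the study. A CACE analysis is foreseen if compliance is too low.

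**The concern.** Stopping a product and stopping observation are different acts, and the withdrawal section merges them. Two of the three triggers are themselves trial outcomes or direct results of them, so whether a patient goes on being observed depends on what is being measured.

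Three things are at stake:

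- **Secondary outcomes.** They are compared only among patients who finish. Those with severe toxicity are, by rule, the ones who do not.
- **Primary outcome.** A patient terminated in cycle 1 for severe neutropenia, say, with no diarrhea so far has an unfinished observation window. The carry-forward rule turns it into a non-event.
- **CACE.** Its estimate needs outcomes from non-compliers, whom the third trigger removes.

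An intention-to-treat label does not bring back data that were never collected.

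**Working it through.** **1. The plan's own figure.** Sample size sets "Considering an estimated dropout rate of 20" percent against about 40 evaluable patients per group: 40 / (1 − 0.20) = 50. This step reproduces, and the allowance is 0.20 × 50 = 10 patients per arm. (The 40 does not reproduce from 37.5% vs 63.4%, two-sided 5%, 80% power; the pooled formula gives 58. That is a separate matter and does not bear on this point.)

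**2. The sections side by side.** A severe chemotherapy reaction leads to a modified schedule under Safety outcomes and to an end of participation under Subject withdrawal criteria. Both can happen in sequence. But then the patient does not finish, leaves the PPS, and the alteration drops out of the analysis meant to compare alterations.

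**3. Selection in the PPS.** Background states that "the incidence of severe diarrhea (grade 3–4) is 11–32" percent. Assume that grade 3–4 diarrhea counts as a severe AE and that severe cases are part of the 63.4% any-grade control rate from Sample size. With severe rate s, the any-grade rate among those left is (0.634 − s) / (1 − s):

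- s = 0.11: 0.524 / 0.89 = 58.9%
- s = 0.32: 0.314 / 0.68 = 46.2%

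Grade 3–4 diarrhea itself becomes zero in both arms, so the rank test on worst grade would compare little beyond grades 0 to 2. Alterations due to severe reactions also become zero.

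The documents give no severe rate under SXD, so the effect on the between-arm contrast can only be shown under assumed values. Without selection the risk difference is 63.4 − 37.5 = 25.9 points and the risk ratio 0.375 / 0.634 = 0.591.

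| Severe, control | Severe, SXD (assumed) | Any-grade left, control vs SXD | Difference (points) | Risk ratio |
|---|---|---|---|---|
| 11% | 5% | 58.9% vs 34.2% | 24.7 | 0.581 |
| 11% | 6.5% | 58.9% vs 33.2% | 25.7 | 0.563 |
| 32% | 10% | 46.2% vs 30.6% | 15.6 | 0.662 |
| 32% | 19% | 46.2% vs 22.8% | 23.3 | 0.495 |

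The risk ratio can move either way. The same selection applies to the PPS check on the primary outcome.

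**4. Carry-forward in the primary analysis.** A patient terminated for severe late diarrhea has already met the any-grade definition and is classified correctly. The exposed patients are those terminated for another reason before any diarrhea. The documents give no rate. Assume a fraction w of each arm leaves this way, unrelated to later diarrhea, and that all their later events are missed. Each arm's rate is then multiplied by (1 − w). Power uses the two-sided pooled normal approximation at 50 per group:

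| w (assumed) | Control | SXD | Difference (points) | Power |
|---|---|---|---|---|
| 0 | 63.4% | 37.5% | 25.9 | 74.3% |
| 10% | 57.1% | 33.8% | 23.3 | 65.2% |
| 20% | 50.7% | 30.0% | 20.7 | 56.2% |
| 30% | 44.4% | 26.2% | 18.1 | 47.4% |

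With equal loss the difference shrinks. If loss differs between arms, the bias can go in either direction.

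**The case against.** The best defence is that less is lost than the withdrawal wording suggests. The triggering event can itself be recorded: a grade 3–4 episode has been graded by the time it leads to withdrawal, and termination is one of the alterations Secondary outcomes counts. Safety outcomes follows AEs until the patient is stable. Only changes due to severe reactions trigger withdrawal, so other alterations stay on study. The article never says that data collection stops, and a full protocol may settle it. CACE is conditional, with no compliance threshold given.

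Most of this stands and narrows the point. It does not cover cycle-2 diarrhea, later alterations or hospitalizations, or the two-cycle response assessment. Nor does recording an event help if the patient is then left out of the PPS on which the secondary analyses rest. That conflict lies between stated rules, so condensation does not explain it.

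A reader might go further and multiply 11–32% by 50, set the resulting 5.5 to 16 patients against the allowance of 10, and conclude that the primary outcome will be missing for more patients than planned. The documents do not support that. Patients with severe late diarrhea are observed primary events. The upper end is also a general range not tied to this regimen. The genotype-specific severe rates in Background, weighted by the 3:1 stratum ratio, give 0.75 × 1/78 + 0.25 × 10/25 = 0.110, or about 5.5 of 50, which is within the allowance.

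A reader might also infer that primary data will be lost unequally between arms. For patients who leave before any diarrhea this is possible but not shown: the earlier SXD results the article reports concern gastrointestinal toxicity and diarrhea, not neutropenia.

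**Conclusion.** The point holds in a limited form. Followed as written, the withdrawal criteria end participation on events that other sections count as on-trial outcomes, and no statement keeps observation going.

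The secondary outcomes are hit hardest. Through the PPS, severe toxicity and the alterations it causes are excluded by construction, and any-grade CRD in a control-rate arm would read 58.9% to 46.2% instead of 63.4%. This rests on grade 3–4 diarrhea counting as a severe AE and on the severe and any-grade rates, which come from different sources, applying to the same patients.

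The primary outcome is harmed only through patients terminated for other reasons before any diarrhea and then carried forward as event-free. Its size is unknown; the 10–30% scenarios are assumptions, not forecasts. The effect on CACE is real but secondary.

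**What to change.** 1. Reword Subject withdrawal criteria so that the three events are recorded as discontinuation of study product, protocol chemotherapy or both. State that diary, CTCAE grading, antidiarrheal use, hospitalization and response assessment continue to the planned end of cycle 2 for every randomized patient unless consent to follow-up is withdrawn. Carry-forward then has little to act on, and non-compliers' outcomes are available for CACE.
2. In Statistical analysis, analyse secondary outcomes in all randomized patients instead of the PPS.
3. Reconcile Subject withdrawal criteria, Secondary outcomes, Safety outcomes, Quality control and Statistical analysis on what a chemotherapy modification means for a patient's status in the study.

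None of this changes a clinical stopping rule or says which one is right. The cost is protocol wording and a modest amount of follow-up for discontinued patients, using visits and diaries already planned. It has to be done while patients are being followed, because data not collected cannot be recovered at analysis.
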